### Intervention

The surgical procedures, as well as hospitalization in the inpatient group, will take place at the UMC Utrecht. Patients in both groups will undergo (revision) stapedotomy under general anesthesia. The surgical procedure will be performed by three surgeons according to standard protocol in the UMC Utrecht [7].

Patients allocated to the conventional group will be admitted one day before or the day of surgery and will be discharged one day after surgery. Patients allocated to the day-case group will be admitted into the outpatient unit one day before or on the day of the surgery and will be discharged the day of the surgery. Patients are not allowed to drive for 24 h following day-case surgery and will be recommended 24 h of relative bed rest. After a period of 24 h, patients can return to their daily routine. Participants will be asked to contact the hospital in case of severe postoperative vertigo or pain. The ear tampon will be removed in the outpatient clinic seven to ten days postoperatively in both groups.

It is to be expected that patients who have been operated on in day-case will sometimes stay overnight, for example due to postoperative nausea or dizziness. If patients are not physically capable of same-day discharge or if surgeons do not support this, patients will stay overnight. These patients will be asked to complete their follow-up and analyses will be carried out on an intention-to-treat basis.

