## Background

Otosclerosis is characterized by abnormal sponge-like bone growth in the otic capsule, causing progressive hearing loss, vertigo and/or tinnitus [1]. It mainly affects the ossicular chain and can be treated surgically by removing (part of) the stapes and replacing it with a prosthesis; stapedotomy and stapedectomy respectively. Numerous surgeons have reported either equal hearing results when comparing stapedotomy and stapedectomy or better results with stapedotomy [2–6]. Although stapes surgery has proven to be a safe and effective treatment option for otosclerosis [7], permanent sensorineural hearing loss can occur and is the most dreaded complication of stapes surgery. The incidence of this complication following primary stapes surgery has been reported to be less than 1 % in large series [8, 9]. Other complications associated with stapes surgery are postoperative vertigo in 12-45 % of patients [10–13] and tinnitus in 8-54 % of patients [14–17].

Currently, in our clinic, stapes surgery involves overnight hospital stay. Many other otologic procedures that involved overnight hospital stay in the past are presently being performed on an outpatient basis successfully [18–20]. Ear, nose and throat (ENT) surgery is well suited to a day-case approach as many of the disease entities are benign and procedures are associated with low complication rates [18]. Even though one of the major drives towards day-case surgery has been financial, other non-financial benefits are of major importance. Day-case surgery is associated with shorter waiting time for surgery and reduced risk of infection [21]. Moreover, as a result of a more rapid social and emotional rehabilitation compared to overnight stay, patients might prefer day-case surgery.

Reports on day-case surgery for otosclerosis are scarce [22, 23]. One prospective case series of 24 consecutive otosclerosis patients undergoing day-case stapes surgery [22] reported a readmission rate of 12.5 percent, reasons being vertigo and asthenia. All of these patients were treated under general anesthesia. One prospective case-control study comparing ten day-case and ten inpatient stapedectomies [23] showed no difference in postoperative hearing thresholds, sensorineural hearing loss, speech audiometry or postoperative vertigo. All procedures were performed under local anesthesia. The authors did not report on quality of life (QoL) following day-case surgery.

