### Sample size calculation and recruitment

To establish equivalence in postoperative mean air conduction of 5 dB (standard deviation 10) between the day-case and the inpatient group with an alpha of 0.05 and a power of 80 %, 51 participants per group are needed. To anticipate on a withdrawal of 10 % of the participants, 5 more participants than needed will be recruited per group. At the ENT department in UMC Utrecht, we perform an average of 80 (revision) stapedotomies per year. Assuming a participation rate of 75 %, we will be able to include the necessary number of 112 patients in two years. If participants wish to leave the study or the investigator decides to withdraw a participant from the study for urgent medical reasons, these participants will not be replaced unless these account for more than 10 %.

Patients will be recruited from the outpatient ENT department of the UMC Utrecht. If an otosclerosis patient meets the criteria for stapes surgery and the inclusion criteria for this study, one of the researchers will explain the content of the study and provide the patient with written patient information and an informed consent form. Patients consent to the use of their data for the research purposes outlined in this protocol, which includes publication of the results once the trial has been completed. Further details can be found in Additional file 1 (informed consent form; translated to English, original in Dutch). Patients that do not want to be included in the study because they want to undergo stapes surgery in a clinical setting will be asked whether they want to fulfill the study procedures and whether their data can be used for analysis.

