### Randomization, blinding and treatment allocation

A web-based randomization program (Julius Center, UMC Utrecht, Utrecht, The Netherlands) shall be used to allocate subjects randomly into two groups with stratification for age. Block randomization will be used with an allocation ratio of 1:1. The randomization chart, including block size, is established before the start of the study by an independent data manager and will not be available to any of the people involved with enrolment or treatment of participants. Consequently, treatment allocation sequence is concealed for participants, care providers and researchers. Blinding of both participants and care providers is not possible, since both participants and care providers will be aware of the surgical setting and hospital stay.

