### Statistical analysis

Baseline characteristics per group will be described as means and standard deviations. Differences in the baseline will be analyzed using the independent samples students *t-*test or non-parametric tests for continuous variables and the Fisher’s exact test for categorical variables.

The primary and secondary outcome data are quantitative and will be presented both continuous and categorical. Between-group mean differences, rate differences and rate ratios with 95 % confidence intervals will be calculated. For further analysis of between-group differences in both primary and secondary outcomes the independent samples students *t–*test or non-parametric tests will be used for continuous outcomes and the Fisher’s exact test for categorical outcomes. Within-subject comparisons will entail differences in mean values and percentages before and after stapes surgery. These will be analyzed using paired *t*-tests for continuous measures and the McNemar test for categorical outcomes.

Missing values will be handled using multiple imputation and all analyses will be performed on an intention-to-treat basis. A sensitivity analysis will be performed using all of the data acquired from patients that opted not to be included in the study, but did fill out the questionnaires and underwent pure-tone audiometric and speech audiometric follow-up.

The data will be reported according to the CONSORT Statement [37, 38].

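### An equivalence trial that expects overnight stays in its day-case arm has only intention-to-treat analyses; a supportive analysis that accounts for conversions should be added

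*Protocol article*

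**What the plan says.** The protocol article (Sample size calculation and recruitment) sets the aim: "To establish equivalence in postoperative mean air conduction of 5 dB (standard deviation 10" dB), and continues "with an alpha of 0.05 and a power of 80 %, 51 participants per group are needed". Five more per group are added for withdrawal; nothing is added for conversion.

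Surgery and anaesthesia are the same in both arms, so what separates them is discharge on the day of surgery against discharge the day after. The Intervention section expects this separation to be incomplete: "It is to be expected that patients who have been operated on in day-case will sometimes stay overnight". The reasons given are the patient's condition or the surgeon's judgement. On how such patients are handled it says: "These patients will be asked to complete their follow-up and analyses will be carried out on an intention-to-treat basis".

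The Statistical analysis section repeats the rule without exception: "all analyses will be performed on an intention-to-treat basis". Its single sensitivity analysis brings in data from people who chose not to be randomised. It does not deal with day-case patients who stayed overnight.

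**The concern.** In a superiority trial, patients who receive the other arm's care shrink the ITT difference and make a positive claim harder. In an equivalence trial the same shrinkage makes the claim easier. A day-case patient who stays overnight has received the feature that defines the inpatient arm. If same-day discharge did affect hearing, each such patient would move the ITT difference towards zero.

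What is at stake is the reach of the conclusion. A finding of equal hearing results will readily be read as a statement about going home on the day of surgery. ITT alone cannot show whether the arms were alike because same-day discharge does no harm, or partly because some of the day-case arm was not discharged the same day.

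**Working it through.** **Inputs.** Margin 5 dB, SD 10 dB, alpha 0.05, power 80% and 51 per group (Sample size calculation and recruitment); 1:1 allocation (Randomization, blinding and treatment allocation); 95% confidence intervals and ITT throughout (Statistical analysis). The conversion proportion c is not given and is varied here. The nearest figure is in the Background, where a cited series of 24 day-case patients "reported a readmission rate of 12.5 percent" (3 of 24). That is readmission, not failure to discharge, so 12.5% serves only as one point in a range.

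**The plan's own figure.** One-sided 5% test: n = 2 × [10 × (1.645 + 0.842) / 5]² = 49.5, so 50 per group. The t-based version gives power 0.799 at 50 and 0.806 at 51, so 51 is reproduced. A two-sided 5% test would give 63.

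**Assumptions for the check.** The true effect of actual same-day discharge lies exactly at the 5 dB margin, and converted patients have the inpatient result. The expected ITT difference is then 5 × (1 − c).

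**Decision rule.** Equivalence is declared if the whole interval lies within ±5 dB. The standard error is 10 × √(2/51) = 1.980. With 100 degrees of freedom the half-width is 1.660 × 1.980 = 3.29 dB for a 90% interval and 1.984 × 1.980 = 3.93 dB for a 95% interval.

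**Hand check at c = 12.5%, SD treated as known.** The expected ITT difference is 4.375 dB.
- 90% interval: the estimate must lie within ±(5 − 3.29) = ±1.71. The probability is Φ((1.71 − 4.375)/1.980) − Φ((−1.71 − 4.375)/1.980) = 0.089 − 0.001 = 0.088.
- 95% interval: the estimate must lie within ±1.07, and the probability is 0.048 − 0.003 = 0.045.

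Allowing for an estimated SD (t-based two one-sided tests) gives the values below.

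| Conversion c | Expected ITT difference (dB) | Chance of declaring equivalence, 90% CI | Same, 95% CI |
|---|---|---|---|
| 0% | 5.00 | 5.0% | 2.4% |
| 10% | 4.50 | 8.1% | 4.1% |
| 12.5% | 4.375 | 9.0% | 4.7% |
| 20% | 4.00 | 12.4% | 6.7% |
| 30% | 3.50 | 18.2% | 10.2% |

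**A per-protocol comparison under the same assumptions.** Removing 12.5% of the day-case arm leaves 45 against 51. The chance of declaring equivalence is then 4.9% with a 90% interval, but only if conversion is unrelated to hearing.

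**Precision of a complier-average estimate.** Dividing the ITT difference by (1 − c) divides its half-width by the same factor. The 95% half-width of 3.93 dB becomes 3.93/0.875 = 4.49 dB at 12.5%, 3.93/0.80 = 4.91 dB at 20% and 3.93/0.70 = 5.61 dB at 30%. The 90% half-widths are 3.76, 4.11 and 4.70 dB. At 30% conversion a 95% interval could not fit within ±5 dB at all.

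**The case against.** The strongest reply is that conversion is not crossover here. The Intervention section writes the overnight stay into the day-case pathway, so a converted patient has followed the protocol. The randomised contrast is planned day-case surgery, with a stay if needed, against planned admission. For that contrast ITT targets the right quantity and conversions do not inflate the error rate. This stands. A reader might infer that ITT is the wrong primary analysis, or that the trial's type I error is really 9%; the documents support neither. The inflation applies only to the effect of actual same-day discharge.

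A reader might also infer that equivalence should be claimed only if ITT and per-protocol analyses both succeed. That goes too far. Conversion follows postoperative symptoms or a surgeon's decision, so a per-protocol set drops symptomatic patients from the day-case arm while inpatients with the same symptoms stay in. If early symptoms go with poorer hearing, the day-case arm is flattered. Such a set can support the primary analysis but is a poor gate.

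The size is also open to challenge. The protocol names a 95% interval, and with it the chance stays below 5% at 12.5% conversion, though it has about doubled from 2.4%. The 12.5% comes from three readmissions. And the protocol does not tie the 5 dB margin to either interval, so neither column of the table is its stated rule.

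Lastly, a supportive per-protocol analysis is often left to an analysis plan that is not shown here. That carries less weight, because the text makes all analyses ITT; a separate plan that added one would depart from it.

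**Conclusion.** The point holds as a limit on what the planned analyses can show, not as an error in choosing ITT. The protocol aims for equivalence, expects the feature that separates the arms to be lost in some day-case patients, and prescribes only an analysis in which that loss favours equivalence as regards same-day discharge itself.

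The size depends on a conversion rate that nobody has stated. Over 12.5 to 30% conversion, the chance of declaring equivalence when same-day discharge has a 5 dB effect is 9 to 18% with a 90% interval and 4.7 to 10.2% with the stated 95% interval, against 5.0% and 2.4% with no conversion. These figures assume an effect exactly at the margin, inpatient-like results in converted patients, SD 10 and 51 analysed per group. With few conversions the effect is small. This is an inexpensive improvement worth making, and it does not invalidate the primary comparison.

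**What to change.** Amend the Intervention and Statistical analysis sections as follows.

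1. Keep ITT as the primary analysis, and state that it addresses planned day-case surgery with an overnight stay if needed.
2. Record discharge status for every participant and report the conversion rate with reasons.
3. Prespecify two supportive analyses of the primary outcome against the same ±5 dB margin:
   - a complier-average estimate, that is, the ITT difference divided by the proportion of the day-case arm discharged the same day, with the assumption stated that assignment alone does not affect converted patients' hearing;
   - a per-protocol comparison of day-case patients discharged the same day with inpatients who stayed overnight, with its selection bias acknowledged.
4. State that if these do not agree with ITT, the equivalence conclusion is limited to the planned day-case strategy and is not extended to same-day discharge itself.

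The cost is a little wording and a small amount of analysis. Converted patients are already kept in follow-up, so their outcomes will be available, and clinical care does not change. The price is wider intervals in the supportive analyses, as shown above; at high conversion they may be unable to confirm equivalence, which is itself worth reporting. The article describes the trial as still recruiting, so all of this could be fixed before results are known.

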### Outcome measures

Evaluation will take place preoperatively and at approximately two months, three months and one year postoperatively by means of pure-tone audiometry, speech audiometry and questionnaires. Vertigo and tinnitus will also be evaluated directly postoperatively. In addition participants will be asked to keep a costs diary for the duration of one year. Questionnaires and costs diaries can be fulfilled digitally or on paper and will be sent via email or mail respectively.

#### Primary outcome measure

Our primary outcome is the postoperative air conduction at approximately two and twelve months postoperatively, as measured by pure-tone audiometry for the following frequencies: 500, 1000, 2000 and 4000 Hz, in accordance with the Committee on Hearing and Equilibrium guidelines for the evaluation of results of treatment of conductive hearing loss [25]. However, thresholds at 3000 Hz were substituted in all cases with those at 4000 Hz, because the 3000 Hz frequency is not part of the standard measurement protocol in the Netherlands.

#### Secondary outcome measures

Our secondary outcome measures include (subjective) hearing improvement, patient satisfaction, QoL, tinntus, vertigo and cost-effectiveness.

### Pure-tone and speech audiometry

Pure-tone and speech audiometry will be performed preoperatively and at approximately two and twelve months postoperatively. Measurements will include mean four-frequency bone conduction thresholds, air conduction thresholds and air-bone gap. The following frequencies will be used to calculate mean thresholds: 500, 1000, 2000 and 4000 Hz. Sensorineural hearing loss will be evaluated using frequencies 1000, 2000 and 4000 Hz. Sensorineural hearing loss is defined as a deterioration in mean bone conduction thresholds exceeding 10 to 15 dB.

Performance on speech audiometry will provide information on word recognition abilities and can, in conjunction with pure-tone audiometry, help determine the degree and type of hearing loss.

### Patient satisfaction

Patient satisfaction will be evaluated using the Utrecht patient satisfaction survey (Additional file 2; translated to English, original in Dutch). This seven-item questionnaire was developed in our center and contains questions regarding the hospital stay. Specifically patients are asked whether they were satisfied with the intervention group that they were allocated to.

### Quality of life

QoL and hearing benefit will be assessed preoperatively and at three and twelve months postoperatively using the following four questionnaires:**-** The Glasgow Health Status Inventory questionnaire: an 18-item questionnaire, which measures the effect of an otologic problem on QoL at the time the questionnaire is completed. Three domains (general, social support and physical health) are measured based on a 5-point Likert scale ranging from high health status to low health status. The total score ranges from 0 to +100.**-** Glasgow Benefit Inventory: an 18-item questionnaire, which measures the change in health status as a result of a surgical intervention. A specific version of the Glasgow Benefit Inventory will be used that has been validated to measure changes in health status as a result of otorhinolaryngological procedures [26]. The same three domains as the Glasgow Health Status Inventory questionnaire are measured according to the 5-point Likert scale. The total score ranges from -100 (maximal negative benefit), through 0 (no benefit), to +100 (maximum benefit).**-** EuroQoL-5D: a five-item questionnaire on mobility, self-care, daily activities, pain and complaints and anxiety or depression that assesses general health status [27, 28]. In addition, the general health status is rated on a visual analogue scale than runs from 0 to 10. A score of 0 equals worst imaginable health state and a score of 10 equals best imaginable health state.**-** Health Utilities Index 3: a fifteen-item questionnaire that measures general health status by evaluating eight domains: vision, hearing, speech, ambulation, dexterity, cognition, emotion and pain [29].

### Tinnitus and vertigo

Tinnitus and vertigo will be assessed preoperatively and at three and twelve months postoperatively using the following four questionnaires. The Utrecht Burden Questionnaire for tinnitus and vertigo will also be administered directly postoperatively in case of direct postoperative tinnitus and/or vertigo:Tinnitus Handicap Inventory: a 25-item questionnaire evaluating three domains: a functional, emotional and catastrophic domain [30, 31];Tinnitus Questionnaire: a 52-item questionnaire evaluating five domains: tinnitus-related emotional and cognitive distress, intrusiveness, auditory perceptual difficulties, sleep disturbance and somatic complaints. The response categories are ‘true’ (0/2 points), ‘partly true’ (1 point) and ‘not true’ (0/2 points), depending on the question. A validated Dutch version will be used [32, 33];Dizziness Handicap Inventory: a 25-item questionnaire evaluating three domains: functional, emotional, and physical aspects of dizziness and unsteadiness. The response categories are ‘yes’ (4 points), ‘sometimes’ (2 points), and ‘no’ (0 points). The total score discriminates between a mild (16–34 points), moderate (36–52 points), and severe (54+ points) handicap. A validated Dutch version will be used [34, 35];Utrecht Burden Questionnaire for tinnitus and vertigo: measures severity and character of tinnitus and vertigo by using visual analogue scales and numerical rating scales (Additional file 3).

### Cost-effectiveness/utility analysis

The difference in costs and benefit will be represented using the Incremental Cost Utility/Effectiveness Ratio (ICUR/ICER). The ICUR/ICER is calculated by dividing the difference in costs by the difference in utility or effectiveness. Effectiveness will be reflected by pure-tone audiometric results. Utility reflects the amount of money that people are willing to pay to achieve a certain health status. Utility scores derived from questionnaires such as the EuroQoL-5D and the Health Utilities Index 3 can be used to calculate the ICUR.

Participants will be asked to keep a costs diary. Participants will fulfill this diary preoperatively and at regular intervals postoperatively. The first month the diary will be fulfilled weekly followed by monthly fulfillment for the duration of one year. Costs will be measured from a societal and health care perspective. Both direct and indirect costs will be collected. Direct costs include hospitalization, surgery, doctor’s visits, and diagnostic tests. Indirect costs include travel expenses and sick leave. The Dutch guidelines for costing research in health economic evaluations, issued by the National Healthcare Institute [36], will be used to calculate unit prices of resources that were used.

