**Discussion/conclusion:**

This trial allows for a comparison between day-case and inpatient stapes surgery to investigate the hypothesis that day-case stapes surgery is associated with a higher quality of life and higher cost-effectiveness, while maintaining equal hearing results, compared to inpatient stapes surgery.

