## Discussion/conclusion

Stapes surgery seems to be a surgical procedure that is well suited for day-case treatment as it has proven to be a safe treatment with low complication rates. However, current literature lacks evidence based recommendations supporting day-case stapes surgery. This randomized controlled trial allows for a comparison between day-case and inpatient stapes surgery to investigate the hypothesis that day-case stapes surgery is associated with a higher QoL and higher cost-effectiveness, while maintaining equal hearing results, compared to inpatient stapes surgery. This is the first high quality trial evaluating and quantifying the benefits of day-case stapes surgery for patients with otosclerosis.

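### Cost per decibel cannot inform the cost-effectiveness hypothesis, because its denominator is the hearing difference that the trial expects to be near zero

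*Protocol article*

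**What the plan says.** The section Cost-effectiveness/utility analysis reduces the economic comparison to one of two ratios: "The ICUR/ICER is calculated by dividing the difference in costs by the difference in utility or effectiveness". For the ICER it fixes the effect measure: "Effectiveness will be reflected by pure-tone audiometric results". For the ICUR it is more permissive: "Utility scores derived from questionnaires such as the EuroQoL-5D and the Health Utilities Index 3 can be used to calculate the ICUR". It gives neither ratio priority. The same section describes utility as follows: "Utility reflects the amount of money that people are willing to pay to achieve a certain health status".

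The section Sample size calculation and recruitment states the aim for hearing: "To establish equivalence in postoperative mean air conduction of 5 dB (standard deviation 10) between the day-case and the inpatient group". The closing Discussion/conclusion gives the hypothesis that "day-case stapes surgery is associated with a higher QoL and higher cost-effectiveness", "while maintaining equal hearing results, compared to inpatient stapes surgery". The abstract says the same of hearing.

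**The concern.** Two stated choices pull against each other. The ICER denominator is the between-group difference in hearing, and the design aims to show that this difference is negligible. A ratio whose denominator is centred near zero has an unstable sign and size. If day-case surgery saves money, chance alone would decide whether the ratio reads as cheaper with better hearing or cheaper with worse hearing.

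Cost-effectiveness is a secondary outcome, but it is one of the two respects in which the trial expects day-case surgery to be superior. If cost per dB were used to judge that claim, the answer would be least informative when the hearing result is as hoped.

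The description of utility is a separate, smaller error. Scores from the EuroQoL-5D and the Health Utilities Index 3 are preference weights for health states. Willingness to pay enters only later, when a gain in utility is given a monetary value.

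**Working it through.** **Inputs**, all from Sample size calculation and recruitment: margin 5 dB, SD 10 dB, alpha 0.05, power 80%, 51 per group, 112 recruited (56 per group).

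**The plan's own figure.** With one-sided alpha 0.05, n = 2 × [10 × (1.645 + 0.842) / 5]² = 49.5, so 50 per group by the normal approximation. The exact t calculation gives 51 (power 80.6%). The stated 51 is reproduced on that basis.

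**Precision of the denominator**, taking mean air conduction as the effect measure:
- SE = 10 × √(2/51) = 1.98 dB (1.89 dB with 56 per group).
- The 95% CI for the hearing difference excludes zero only if the observed difference exceeds 1.96 × 1.98 = 3.88 dB.

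**Sign and interval of the ICER.** The 95% Fieller set for a ratio is unbounded whenever the 95% CI of its denominator includes zero. With d the true difference, the probability of the wrong sign is Φ(−d/SE), and the probability of an unbounded set is Φ(1.96 − d/SE) − Φ(−1.96 − d/SE).

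| True difference | Hearing difference has wrong sign | 95% Fieller set unbounded |
|---|---|---|
| 0 dB | 50% (no true sign; coin flip) | 95.0% |
| 2 dB | 15.6% | 82.7% |
| 5 dB | 0.6% | 28.6% |

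The middle column concerns the denominator. It carries over to the ICER when the sign of the cost difference is well determined. At a true difference of 0 the ICER sign is 50/50 whatever the costs are.

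**Link to success on hearing.** Equivalence by two one-sided tests requires the 90% CI to lie within ±5 dB, so the observed difference must be below 5 − 1.645 × 1.98 = 1.74 dB. That is less than 3.88 dB. Every trial that meets equivalence on this test therefore has a denominator whose 95% CI includes zero. With 56 per group the two limits are 1.89 and 3.70 dB, and the conclusion is the same. It holds whenever 5 − 1.645 SE < 1.96 SE, that is SE > 5/3.605 = 1.387 dB, or fewer than 200/1.387² ≈ 104 per group.

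**Spread of the ratio.** The documents give no cost figures, so these are assumptions in arbitrary cost units. In simulations at a true hearing difference of 0, the 2.5th to 97.5th percentiles of cost per dB were:
- cost difference −500 (SE 200): about −4,000 to +4,000;
- cost difference −1,000 (SE 300): about −7,900 to +8,100;
- cost difference −1,000 (SE 1,000): about −9,500 to +9,400.

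**The case against.** The strongest reply is that cost per dB is only one of two planned ratios. The ICUR divides by a utility difference, and the trial expects quality of life to be better after day-case surgery, so equal hearing does not put that denominator at zero. This stands. A reader might infer that the whole economic evaluation fails; the documents do not support that.

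Second, the section Statistical analysis already plans between-group mean differences with 95% confidence intervals for secondary outcomes. On a natural reading this includes costs and effects, so readers would not be left with the ratio alone. This also stands, and it limits the harm.

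Third, the audiometric measure for the ICER is not specified. Pure-tone and speech audiometry lists bone conduction and air-bone gap as well as air conduction. The percentages above belong to air conduction, the only measure with a stated SD. It is, however, the primary outcome and the one sized for equivalence.

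Other stronger readings should also be set aside:
- **Money divided by money.** The next sentence takes utility from two questionnaires, so the definition is a wording error that changes no computation.
- **No QALYs.** The text does not exclude them, and a full protocol, said to be in the trial register, is not shown here.
- **Rank tests on costs.** Nothing assigns a rank test to costs; the general rule puts mean differences first.
- **An undefined ratio.** That is literal only at a difference of exactly zero; the practical problem is instability.

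**Conclusion.** The point holds for the ICER. Cost per dB, as defined, cannot inform the cost-effectiveness hypothesis when the trial succeeds on hearing. This rests on air conduction as the effect measure, the planning SD of 10 dB, approximate normality of the mean difference, and equivalence judged by two one-sided tests at 0.05 each.

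The ICUR is not invalidated. It would share the problem if the utility difference were also small, which is possible: after baseline, the questionnaires are given at three and twelve months, whereas the expected benefit is attributed to rapid discharge and rehabilitation. The documents give no SD or expected difference for utility, so this cannot be quantified.

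The definition of utility is wrong as written. Both matters concern a secondary outcome, leave the primary analysis untouched, and should be corrected before analysis.

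**What to change.** 1. Do not use cost per dB as a decision statistic.
2. Make the utility-based analysis the main economic result, expressed as incremental net monetary benefit, λ × ΔE − ΔC, where ΔE is the utility-based effect, ΔC the cost difference and λ the willingness to pay, over a stated range of λ. This quantity is well defined when ΔE is zero.
3. Report incremental cost and incremental effect separately with confidence intervals, and show them on a cost-effectiveness plane or as an acceptability curve.
4. Do not switch to cost-minimisation because hearing is equivalent. A quality-of-life difference is hypothesised, so equal hearing alone does not make the two settings equal in effect.
5. Reword the utility sentence: the EuroQoL-5D and Health Utilities Index 3 give preference weights, and willingness to pay is applied only when the result is valued.

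The cost is a change of wording and a little extra analysis on data already being collected.
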